Another factor influencing social interactions is the direction of gaze (15). Eye-tracking reveals that children with ASD show aberrant patterns of gaze and fixation times when seeing human faces (16, 17) and eye gaze abnormalities have even been proposed as a robust biomarker for ASD (16). Moreover, dysfunctions in several brain regions including the dorsolateral prefrontal cortex (DLPFC) are involved in the development of this aberrant gaze behavior. In typically developing individuals, direct gaze leads to an enhanced response in brain areas important for empathic processes like theory of mind (ToM). In contrast, individuals with ASD show the same response when the gaze is averted and respond to direct gaze with an abnormal activation of the ToM network [medial prefrontal cortex (MPFC), temporoparietal junction, posterior superior temporal sulcus region, and amygdala] (15). These regions are also part of the social brain network (SBN) (18, 19).

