#### Neurophysiological Measures

**EEG data acquisition:** EEG data will be collected from 19 cortical sites (Fp1, Fp2, F3, F4, F7, F8, Fz, FCz, C3, C4, Cz, T5, T6, P3, P4, Pz, O1, O2, and Oz) positioned according to the international 10-20 system using Ag/AgCl electrodes and the Thera Prax Q-EEG System (NeuroConn, Illmenau, Germany). Electrode-skin impedance will be kept below 3 kΩ.

**Resting-state EEG:** Neural oscillations will be recorded in eight 1-min trials, four with eyes-closed (C) and four with eyes-open (O). A guideline-based counterbalanced order (COCO-pause-OCOC) will be used considering disorder-specific characteristics such as a discomfort with longer eyes-closed intervals and minimizing the risk of participants falling asleep in the eyes-closed condition (113, 114).

**MRI data acquisition:** Functional and structural whole-brain imaging will be conducted using a 3-T Siemens MAGNETOM Prisma MR Scanner (Siemens, Erlangen, Germany) equipped with a 64-channel head coil.

**Resting-state fMRI:** RS data will be acquired for 7 min using an echo-planar imaging sequence with the following parameters: TE/TR = 35/728 ms, field of view (FoV) = 192 × 192 × 144 mm, matrix size = 96 × 96, 72 slices, multiband factor = 8, resulting in an isotropic voxel size of 2 mm, flip angle = 55° (optimized Ernst angle), and bandwidth = 3,365 Hz/Px [sequence optimized according to (115)]. To reduce head motion and participant drowsiness, the movie *Inscapes* (116) will be shown during resting-state recordings. This non-social movie features abstract shapes and was developed for the use with children and clinical populations to increase compliance while minimizing cognitive demand (116).

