### Outcomes

The primary outcome will be a reduction in ASD symptoms from baseline in the experimental group compared to the sham group. ASD symptoms will be quantified by the raw score of the German version of the SRS (83) assessed by the primary caregiver.

The secondary outcomes will be increased social cognition and emotion recognition quantified by the raw scores of the MASC (105) as well as correct classifications in the ERT and the FEFA 2 (120). Regarding gaze behavior, longer fixation duration on the eyes and increased pupil dilation will be the outcomes on the MASC and ERT. Outcomes on participants and caregiver ratings will be a decrease in ASD symptoms measured with the ATEC (95) and SCQ (96) and an increase in empathy and emotion regulation abilities measured with the ERQ (97), IECA (98), BES (99), GEM (100), and ERC (101). Neurophysiological activity will be measured at baseline and after the intervention using resting-state EEG and fMRI to measure changes in functional connectivity and electrical activity in the brain. We expect an increased resting-state alpha-power, a decrease in the other frequency bands, and an increased connectivity within the ToM network and DMN. An increased regional activation in key areas of the SBN will be the outcomes during the FHA and ERT.

The exploratory outcomes will include participant and caregiver ratings on comorbid symptoms of ASD using the DISYPS III (102). The brain activation in regions involved in emotion recognition processes and cognitive empathy during emotion recognition with the ERT during fMRI will also be examined exploratorily.

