Basic fMRI processing will be conducted according to (124) using Statistical Parametric Mapping [SPM; (125)]. To counteract the expected high level of in-scanner motion, PESTICA/SLOMOCO (126, 127) and the BrainWavelet toolbox (128) will be used for additional movement and artifact correction. Spatial normalization will be performed to a custom template created using the CerebroMatic toolbox (129) to avoid implausible deformation to match the usual standard adult brain. Subject-level analysis will be conducted using the general linear model in SPM. The FHA task will be modeled according to (118, 130). The ERTs will be modeled as block designs with a single condition. For the morphing variant, the reaction times will be included as a parametric modulator to uncover the possible influence of the subjective strength of the perceived emotion. The RS data will be analyzed by means of seed-based functional connectivity. Since the ERTs constitute newly implemented paradigms, interesting regions of their baseline activation will be used as seeds here. Nuisance regressors for the linear models will be derived *via* the CompCor (131) and Friston-24 (132) approaches with an additional bandpass applied to the RS data. Group-level analyses of fMRI data will be conducted using the Flexible Factorial module in SPM. The time-by-treatment interaction effects will be tested at *p* < 0.05 family-wise error corrected at the peak level and with a primary threshold of *p* < 0.001 uncorrected at the cluster level.

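### The secondary task-fMRI outcome concerns key social brain areas, but the stated family-wise test is not limited to them, which costs power and leaves the choice of areas open

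*Protocol article*

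**What the plan says.** All references are to the protocol article.

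- **Outcomes** sets a regional outcome with a direction, among the secondary outcomes: "An increased regional activation in key areas of the SBN will be the outcomes during the FHA and ERT". It does not list the areas. The next paragraph also places brain activation during the ERT among the exploratory outcomes.
- **Statistical Analysis** gives one decision rule for the group-level maps. The model is fixed ("Group-level analyses of fMRI data will be conducted using the Flexible Factorial module in SPM"). On error control, the article says that "time-by-treatment interaction effects will be tested at *p* < 0.05 family-wise error corrected at the peak level". The same sentence goes on to a cluster-level clause, with p < 0.001 as its primary threshold and the word uncorrected attached. No mask, region of interest or small-volume correction is given for the task data. The only regions selected there are seeds for resting-state connectivity.
- **Neurophysiological Measures** describes the acquisition: "Functional and structural whole-brain imaging will be conducted".
- **Introduction** names candidate areas: the medial prefrontal cortex (MPFC), "temporoparietal junction, posterior superior temporal sulcus region, and amygdala". It says that these also belong to the SBN. The Intervention section reports simulated field peaks at the MPFC.
- **Sample Size Calculations** concedes that the secondary outcomes are underpowered.

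**The concern.** The outcome asks whether named parts of the brain respond more under active stimulation than under sham. The rule as published corrects for a search that is not confined to those parts. The threshold therefore pays for tissue that the hypothesis does not concern, and a true regional effect is more likely to be missed.

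There is also an interpretive cost. The key areas are not listed with the outcome, and the Introduction gives overlapping but different sets: one paragraph names four areas, and the next adds the ventrolateral prefrontal cortex. A peak that survives could be assigned to the SBN once its position is known. The neural claim for the FHA and ERT rests on this test, so both an uninformative null map and a positive map open to later labelling would matter.

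**Working it through.** **The plan's own figure.** None is given for fMRI. The total of 20 was derived for the Social Responsiveness Scale and is used here only to fix the group size.

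**Inputs from the article.** N = 20; imaging at two time points ("Neurophysiological activity will be measured at baseline and after the intervention using resting-state EEG and fMRI"); interaction tested in a Flexible Factorial model; cluster-forming threshold p < 0.001.

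**Inputs assumed.** Equal allocation (10 per arm), effect size, image smoothness, and the number and size of regions. The article gives none of these.

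**Step 1: reduce the test.** With two time points and two arms, the interaction equals a two-sample t test on the pre-post change, with 20 − 2 = 18 df. For a standardised difference in change d, the noncentrality is d × √(10/2) = d × √5.

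**Step 2: a benchmark for d.** The sample-size section uses f = 0.25. For a 2 × 2 interaction with correlation ρ between occasions, d = 4f / √(2(1 − ρ)). At ρ = 0.5 this is 1.00 / √1 = 1.0; at ρ = 0.7 it is 1.00 / √0.6 = 1.29. The article does not state ρ, and its f refers to the clinical scale, so this is only a yardstick.

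**Step 3: one location, d = 1.15.** Noncentrality is 1.15 × 2.236 = 2.57.

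| Criterion | Power |
|---|---|
| two-sided 0.05 | 68% |
| two-sided 0.05/4 | 44% |
| two-sided 0.05/8 | 34% |
| T > 6.8 (a simulated whole-brain peak threshold for 1.4 L) | 0.2% |

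This overstates the contrast, because a map test takes the best voxel in a region. Step 4 allows for that.

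**Step 4: simulated maps.** Settings: 10 per arm, search volume 1.08 L, smoothness 10 mm FWHM, true effect in one region of 10 mm radius. All 5% family-wise thresholds were taken from 1,000 null maps: T = 6.38 for the unrestricted peak, T = 4.24 for the peak within six such regions (22 cm³), and a cluster extent of 12 voxels of 4 mm. There were 400 runs per effect size, so the standard error near 65% is √(0.65 × 0.35/400) = 2.4 points.

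| d | Peak, unrestricted | Cluster FWE, unrestricted | Peak, six regions | Six regions minus cluster |
|---|---|---|---|---|
| 0.8 | 1% | 7% | 39% | 32 points |
| 1.0 | 8% | 20% | 65% | 45 points |
| 1.2 | 14% | 39% | 81% | 42 points |
| 1.5 | 37% | 76% | 97% | 21 points |

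A repeat with fresh random numbers gave the same ordering and similar gaps. The unrestricted peak figure at d = 1.5 was the least stable.

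**Step 5: sensitivity to mask size.** Random-field peak thresholds on 18 df, for smoothness of 6 to 12 mm:

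| Search volume | Threshold T |
|---|---|
| 1.2-1.5 L | 7.1 to 8.7 |
| 100 cm³ mask | 5.5 to 6.8 |
| 50 cm³ mask | 5.1 to 6.4 |

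At any one smoothness the restricted threshold is lower, but the gain shrinks as the mask grows.

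**The case against.** **The search volume is inferred.** The article uses the term whole-brain for the acquisition, not for the correction, and a full protocol or SAP may fix a mask. This stands as a limit: a reader might take unrestricted correction as the stated plan, and it is not stated. However, the article goes down to error-rate type, inference level and cluster-forming threshold. A peak-level family-wise threshold has no value without a search volume. With none named, the analysed image is the natural reading.

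**The test is valid.** A reader might infer that the rule tests only for no interaction anywhere and so cannot answer the question in Outcomes. That is not so. Peak-level family-wise control is strong and localised, so a significant peak in the MPFC or amygdala does support the outcome. Nothing in the article says that a peak elsewhere would count. This objection stands in full.

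**There is some power.** A reader might say that the rule has almost none. That fits the peak test for moderate effects. It ignores the cluster clause, which reaches 76% at d = 1.5 if clusters are family-wise corrected. The wording does not settle whether they are.

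**Low power is already conceded.** That sentence concerns sample size. It is no reason to choose a threshold that gives up more power when a better-matched one needs no extra data.

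**Stimulation effects may spread to distant regions**, as the Introduction says, so an unrestricted search has a purpose. It does, and keeping that map as exploratory serves it.

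**Conclusion.** The mismatch holds in a limited form. The outcome is regional and directional; the published rule is not limited to the regions, and the regions are not listed with the outcome. The consequences are avoidable loss of power and room to label a finding afterwards. They are not an invalid test or a wrong hypothesis.

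Under the simulation's assumptions, restriction gains 21 to 45 points over the more favourable cluster reading for d between 0.8 and 1.5. The sizes depend on effect size, smoothness, region extent and region count, none of which the documents give, and a larger mask would gain less. Restriction came out ahead at every effect size simulated. The point concerns one secondary outcome and should be corrected, but it does not affect the primary analysis.

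**What to change.** In Outcomes and Statistical Analysis:

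1. List the key SBN areas before unblinding, starting from the four in the Introduction (MPFC, temporoparietal junction, posterior superior temporal sulcus region, amygdala).
2. Test the FHA outcome as the active-versus-sham time-by-treatment interaction within that mask. Use small-volume family-wise correction, or the mean contrast estimate per region with Holm adjustment across regions.
3. State the expected direction: a greater increase under active stimulation.
4. Decide whether ERT activation is secondary or exploratory. Apply the same test if it stays secondary.
5. State whether clusters formed at p < 0.001 are then family-wise corrected.
6. Report the unrestricted map as exploratory, and do not count effects outside the mask as support for the SBN outcome.

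The cost is wording and a mask, with no new scans or participants. There are two small downsides: effects outside the named areas become exploratory, and the mask must be brought to the custom template that the article uses for normalisation.

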## Discussion

This study protocol presents the design of an RCT investigating the therapeutic effects of repeated sessions of anodal tDCS over the left DLPFC using a combined approach of EEG, fMRI, and eye-tracking data as well as clinically relevant scores from participants and caregivers. Therefore, the results of this study will elucidate the changeability of aberrant activity through neurostimulation on multiple levels.

An important determinant of stimulation effectiveness is the placement and size of the electrodes (133, 134). Accordingly, and in contrast to previous tDCS studies in children and adolescents with ASD, our study utilizes a parameter configuration based on computational modeling using MRI scans from adolescents with ASD for the simulations.

Another contrast to previous investigations is the use of an intra-stimulation training aiming specifically at improving social cognition and emotion recognition. The training is designed to not only motivate the participants and standardize what they are doing during the stimulation, but also to evoke activity in the target regions of the stimulation. To account for different levels of skills among the participants and to increase ecological validity, the task involves emotion recognition at different levels of difficulty using basic and complex emotions that will be presented isolated or in a dynamic social scene. Moreover, the repeated examination of emotion recognition performance will provide important information about learning curves and session-by-session changes. This may guide future projects in deciding about the ideal number of stimulation sessions, as studies investigating the cumulative effects of tDCS over several days are sparse. Furthermore, there is not much evidence available about the long-term effects of this treatment method. By including two follow-up measures, this study will provide information about the persistence of treatment effects regarding the clinical symptomatology up to 6 months after the end of the intervention.

Within this project, it will also be monitored how the participants react to the stimulation using the questionnaire of sensations related to transcranial electrical stimulation. Even though the safety of tDCS in pediatric populations has been demonstrated repeatedly (92), information about how this patient group perceives and tolerates the mild adverse events of tDCS seems warranted. Individuals with ASD often suffer from sensory hypersensitivity (135) and may thus respond differently to the stimulation.

In this trial, a standard bipolar tDCS montage will be used with the anode placed over the DLPFC targeting the MPFC. However, other montages or stimulation methods such as multi-electrode tDCS or repetitive transcranial magnetic stimulation (rTMS) are also of interest for this population. Here, this established bipolar direct current protocol was chosen as it has milder side effects, has no history of reported serious adverse effects, and is noiseless compared to rTMS (91, 92, 136, 137). Therefore, it might be better tolerated in individuals with ASD, and participants will not be distracted from the intra-stimulation training by potentially painful sensations or sound. Regarding the usage of tDCS as a clinical treatment, a bipolar tDCS has the advantage of being more affordable, portable, and easy to administer, and it opens the possibility for home use in the future. A comparison of the effects of different stimulation protocols as well as stimulation sites is an essential element for future studies.

During the intervention, participants will have daily contact with the study team and undergo the intra-stimulation training. Although these factors could have a beneficial effect on ASD symptoms and emotion recognition skills, the double-blind design and randomization to either active or sham tDCS treatment should mitigate this potential bias.

In conclusion, children and adolescents with ASD are in need of an effective treatment, and modulating brain activity could be a first step toward a new efficient intervention. This neurophysiologically based approach benefits from being non-invasive, being easy to administer, and having only mild and transient side effects (92, 138). TDCS further aims to overcome shortcomings of traditional interventions, such as often long and expensive treatment periods (5). Taken together, this study will provide information about the efficacy of tDCS and the potential to establish it as an affordable alternative or additive treatment for individuals with ASD in the long run.

## Trial Status

The described trial is ongoing, and recruitment commenced in July 2019. Recruitment and interventions had to be paused due to COVID-19 restrictions from March 13, 2020 to June 15, 2020. The data collection will continue until 20 participants completed all 10 intervention sessions and the corresponding pre- and post-measurements. Follow-ups will be conducted 1 and 6 months after the stimulation sessions to investigative long-lasting effects.

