#### Randomization

A total of 20 male participants will be included. To balance the experimental and control group with respect to comorbidities, all participants will be stratified into one of three subgroups based on their clinical presentation: subgroup A for participants without comorbidity, subgroup B for participants with depression as primary comorbidity, and subgroup C for participants with ADHD and/or conduct disorder as primary comorbidity. After subgroup stratification, the participants will be randomly allocated to the active condition or the sham condition by assigning a code to each participant. To ensure a quick study start for the participants after enrollment, a block randomization design will be used.

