#### Blinding

The study mode of the stimulation device encodes sham and active stimulation using preprogramed codes so that the participant and investigators will be blind to the type of stimulation. The stimulation parameters (duration, fade-in, fade-out time, and current intensity) are set and saved on the device to avoid accidental modification of the parameters. To investigate the success of the subject-blinding, participants will be asked about their beliefs of the received stimulation type at the last stimulation session. After completing the 6-month follow-up measurement or after dropping out of the study, participants, and their caregiver will be informed about group allocation. Participants in the sham condition will not receive active stimulation after the end of the trial. Premature unblinding using prepared envelopes can be performed when knowledge of the actual group allocation becomes necessary for the safety of the patient. The blinding, code storage, and preparation of code-break envelopes will be done by a staff member not directly involved in the intervention and the day-to-day management of the study.

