#### Safety and Adverse Events

As for potential risks of tDCS, guidelines report no serious adverse events in over 18,000 sessions of low-intensity transcranial electrical stimulation in pediatric and adult patients, as well as in healthy subjects (89). Current data also specifically emphasize the feasibility, tolerability, and safety of tDCS in children and adolescents (45, 63, 90). Adverse effects of tDCS in children and adolescents were described as mild and transient, including tingling (11.5%), itching (5.8%), redness (4.7%), and scalp discomfort (3.1%) (91). Thus, when guidelines are followed, tDCS is a safe modality for children and adolescents with various neurological conditions (92). The proposed parameters of this study (including electrode size, current strength, and duration) were previously tested for their safety in children younger than the participants in this study (93, 94). The brain stimulation device will be operated by experienced psychologists, neuroscientists, and research assistants trained in the application. Therefore, no serious adverse events or serious health risks for the participants of this study are expected. In the case of a serious adverse event, the participant will be excluded from the trial and the adverse event will be reported to the ethics committee of the Medical University of Vienna and to the Austrian Agency for Health and Food Safety (AGES). To protocol adverse effects, the German version of the questionnaire of sensations related to transcranial electrical stimulation will be used at the last stimulation session (accessible at: http://neurologie.uni-goettingen.de/downloads.html).

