### Statistical Analysis

For the statistical analyses, repeated measures analysis of variance (ANOVA) and hierarchical linear models (HLMs) will be used. A 4 × 2 mixed ANOVA (primary outcome as dependent variable) with *Time* (pre vs. post vs. follow-up 1 vs. follow-up 2) as the within-subjects factor and *Group* (experimental vs. control group) as the between-subject factor will be conducted to investigate an interaction between time and group. In order to test specific effects, *post-hoc* tests will be employed. A HLM will be formulated to investigate time-dependent changes and group differences in task performance across stimulation sessions. A *p* < 0.05 will be considered statistically significant. Analysis will be conducted in *R* (121).

For the eye-tracking data, analysis of fixation duration and pupil dilation will be done in Tobii Studio 3.4.5 (107) following the preprocessing pipeline of other studies using eye-tracking to investigate emotion recognition and social cognition in adolescents with ASD [for the ERT (17) and for the MASC (106)]. These results in a fixation duration on the specified area of interest (AOI) and a measure of average pupil dilation per video. Further analysis regarding pre–post comparisons of AOIs and pupil dilation will be done in *R* (121) using linear models.

For the EEG data, we will employ the *MNE* library (122) written in *Python* (123) to execute data pre-processing, segmentation, and frequency and connectivity analyses. The raw EEG data of each participant will be segmented into epochs of 2 s. A multi-taper method with adaptive weights will be applied to each epoch to obtain power spectral density (PSD) values in each frequency band of interest. Frequency bands of interest will be delta (0.5–4 Hz), theta (4–8 Hz), and alpha (8–12 Hz). Subsequently, PSD values in each frequency band will be averaged across epochs separately for each participant, measurement occasion, and experimental condition.

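### The stated recruitment, exclusion and analysis rules point towards a completer analysis of the SRS and do not protect the comparison of all randomised participants

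*Protocol article*

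**What the plan says.** Five parts of the protocol article bear on who enters the primary comparison.

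- **Number of participants.** Randomization: "A total of 20 male participants will be included". Trial Status: "The data collection will continue until 20 participants completed all 10 intervention sessions and the corresponding pre- and post-measurements". The sample size section arrives at 20 and mentions no allowance for dropout.
- **Serious adverse events.** Safety and Adverse Events: "In the case of a serious adverse event, the participant will be excluded from the trial".
- **Primary analysis.** Statistical Analysis sets a 4 × 2 mixed ANOVA on the SRS with time ("pre vs. post vs. follow-up 1 vs. follow-up 2) as the within-subjects factor") and with group "as the between-subject factor will be conducted to investigate an interaction between time and group".
- **Hierarchical model.** The same section gives this model a different job: "A HLM will be formulated to investigate time-dependent changes and group differences in task performance across stimulation sessions". It is not assigned to the SRS.
- **Rater and disclosure.** Under Outcomes, the SRS is "assessed by the primary caregiver". Under Blinding: "After completing the 6-month follow-up measurement or after dropping out of the study, participants, and their caregiver will be informed about group allocation".

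**The concern.** Completing ten sessions, attending a follow-up visit and having a serious adverse event all happen after randomisation. Choosing the analysed participants by such events can undo the balance that randomisation gave, if the events depend on arm and on outcome.

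The article gives a reason why they might depend on arm. Active stimulation runs at 2 mA for 20 minutes, against 40 seconds plus ramps under sham. The Discussion adds that sensory hypersensitivity is common in this population and may alter the response to stimulation. Dropout over tolerability could therefore differ between arms.

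Two things are at stake. One is precision: the sponsor can meet the recruitment rule in full and still have fewer than 20 participants in the primary test, because the rule ends at the post-measurement. The other is bias: with about ten per arm, one or two selective losses are a visible share of an arm.

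**Working it through.** **Inputs from the article.** N = 20, f = 0.25, alpha = 0.05, target power 80%, two groups, four occasions.

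**Assumptions, because the article gives no figure.** 1:1 allocation, correlation between occasions (rho) of 0.5 or 0.6, sphericity, and the rates and patterns of loss used below.

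**The plan's own figure.** For the time-by-group interaction, with m = 4 occasions and k = 2 groups, the noncentrality is lambda = f² × N × m / (1 − rho), with df1 = (k − 1)(m − 1) = 3 and df2 = (N − k)(m − 1).

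- rho = 0.5, N = 20: lambda = 0.0625 × 80 / 0.5 = 10, df2 = 54, power 0.727. Reaching 80% needs N = 24.
- rho = 0.6, N = 20: lambda = 0.0625 × 80 / 0.4 = 12.5, power 0.827. N = 20 is then enough.

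The stated 20 is attainable but cannot be confirmed, as no correlation is given. That is a separate matter.

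**Loss of precision.** If 10% miss each follow-up independently, 20 × 0.9 × 0.9 = 16.2, so about 16 have all four scores. At N = 16, lambda is 0.0625 × 64 / 0.5 = 8 or 0.0625 × 64 / 0.4 = 10, with df2 = 42. Power over a range of complete cases:

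| Complete cases | rho 0.5 | rho 0.6 |
|---|---|---|
| 20 | 0.73 | 0.83 |
| 18 | 0.67 | 0.78 |
| 16 | 0.61 | 0.72 |
| 14 | 0.54 | 0.65 |

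Eighteen is the result if the same 10% miss both visits.

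**Bias, simple form.** Suppose an arm randomises 10 + k, k of them stop and are replaced, and those k would have scored d SD worse than the 10 who complete. The completer mean then differs from the mean of all randomised by d × k / (10 + k).

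- d = 1, k = 1: 1/11 = 0.09 SD
- d = 1, k = 2: 2/12 = 0.17 SD
- d = 1, k = 3: 3/13 = 0.23 SD

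If both arms lose the same k with the same d, the two shifts cancel and the between-arm bias is zero.

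**Bias, deliberate worst case.** A simulation with no true effect (rho = 0.5, ten completers per arm, 8,000 runs) removed those with the worst pre–post change from the active arm only. Losing 1, 2 or 3 gave a spurious benefit of 0.16, 0.27 or 0.37 SD and a type I error of about 0.06, 0.08 or 0.10. With no loss the type I error was 0.048. With two lost from each arm the between-arm bias was about zero (0.01 SD). The rejection rate in that run was 0.067, so balanced selection removes the bias but does not leave the test wholly undisturbed.

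**The case against.** A reader might infer that the article defines its primary data set as the completers and that the randomised comparison is therefore lost. The documents do not support that. The sentence under Trial Status is a recruitment rule and does not say that data from participants who stop are discarded. Recruiting past a target to cover dropout is compatible with analysing everyone randomised. No analysis set is named, and a condensed article may properly leave that to a statistical analysis plan or full protocol.

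Three further points count for the plan. Deletion of incomplete cases is how a mixed ANOVA usually behaves, not a rule that the text states. The serious-adverse-event route may be empty: the article cites none in over 18,000 sessions and expects none here. And nothing is lost if nobody drops out.

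All of this stands, and it limits the conclusion to a risk. It does not remove the point. The two counts of 20 conflict within the article, and the four-visit ANOVA is fixed there. A later analysis plan can name an analysis set, but it cannot recover SRS scores that were never collected from excluded participants.

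A second objection concerns the remedy. Asking caregivers of dropouts for further SRS ratings would, under the present Blinding section, bring in ratings from people who have been told the allocation. That is correct, so the disclosure rule has to change together with the analysis.

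**Conclusion.** The concern holds in a limited form: taken together, the stated rules favour a completer analysis and do not protect the all-randomised comparison.

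The conflict between 20 included and 20 completing, and the gap between the completion rule and the four visits analysed, are plain from the text. The loss of precision (power down by about 0.11 to 0.12 when 16 remain) rests on an assumed 10% loss per follow-up, an assumed correlation and standard case deletion. The bias of 0.09 to 0.23 SD rests on one-sided loss with replacement in the same arm and a 1 SD worse outcome, none of which the article states. With balanced loss it is about zero. The comparison is at risk in proportion to loss that depends on arm and outcome, and it is intact if there is no such loss.

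**What to change.** 1. Reconcile Randomization with Trial Status by stating separately the number to be randomised and the number expected to complete. For orientation, 20 / (1 − d) gives 23, 25 or 29 randomised for an assumed dropout d of 10%, 20% or 30%.
2. Replace the four-visit ANOVA for the SRS by a likelihood-based mixed model for repeated measures on all randomised participants as allocated, with visit, arm, arm × visit and baseline SRS, and small-sample degrees of freedom. With baseline as a covariate, the modelled visits are post and the two follow-ups, and the arm terms together carry what the ANOVA interaction was meant to test. The model keeps partial data and relies on missingness being explained by the observed data.
3. Reword the safety section so that, whatever is decided clinically about stimulation, the caregiver SRS is still collected with consent.
4. Amend Blinding so that allocation is not disclosed to the caregiver of a dropout until the last SRS has been collected, unless safety requires it.
5. Report the completer analysis as a sensitivity analysis.

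The cost is a slightly more complex model in software already planned (R), a few extra questionnaires, and later disclosure of allocation to those who drop out.
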